#### 2.12.1. Primary Outcomes

Pre-service ECEs’ physical activity and sedentary behaviour-related self-efficacy and knowledge will be evaluated using two (self-efficacy, knowledge) linear mixed effects models wherein group and time are our primary fixed effects. Demographic variables will be used as predictors of pre-service ECEs’ self-efficacy, knowledge, and behavioural intention and perceived behavioural control in our analyses. Specifically, we will explore the extent to which province/territory predicts the dependent variables, and whether there is a significant effect of previous training, early childhood education program type, and mode of delivery. Based on previous research, the pre-service ECE population is largely female [19], so gender-based differences will not be explored. Finally, if baseline differences are observed, we will include student age, physical activity, and sedentary time as covariates in all models. 

#### 2.12.2. Secondary Outcomes

Behavioural intention and perceived behavioural control will be evaluated using a linear mixed effects model, with group and time as fixed effects. As was the case in our primary outcome, we will evaluate the extent to which early childhood education program type, and the province or territory in which the program is situated, impact on our prediction models—and will also include student age, physical activity, and sedentary time as model covariates, if appliable. For the process evaluation, website metrics, and CFIR checklist, data will be explored using descriptive statistics. Thematic analysis [46] will be used to analyse open-ended questions from the process evaluation surveys and the interview transcripts. In line with Guba and Lincoln’s recommendations, steps will be taken to ensure data trustworthiness (e.g., credibility, transferability, dependability, and confirmability; [47]).

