## 2. Methods

### 2.1. Study Design

A mixed-methods quasi-experiential design will be employed to test the effectiveness of the TEACH e-Learning course at improving pre-service ECEs’ physical activity and sedentary behaviour-related self-efficacy and knowledge. Purposefully selected English-speaking colleges/universities offering an early childhood education program in Canada (i.e., clusters) will be randomly assigned to the experimental (*n* = 9) or comparison (*n* = 9) condition. A 4-module e-Learning course (hosted on a secure learning management system platform) will be implemented by schools assigned to the experimental condition, while comparison schools will continue with their typical curriculum. Data will be collected at baseline, post-course completion, and 3-month follow-up. The study protocol and tools for the study have been approved by the Non-Medical Research Ethics Board (initial REB# 116816; January 2021) at Western University and ethics approval for the full-scale implementation will be sought prior to recruitment and data collection. Additional approval from participating college/university ethics boards will be completed, if requested

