### 2.5. Recruitment and Allocation

#### 2.5.1. Universities and Colleges with ECE Programs

To help ameliorate potential recruitment challenges and secure a diverse sample with representation from a number of Canadian provinces, we will draw on our established rapport with early childhood education post-secondary programs and will purposefully select colleges/universities (see sample size explanation below) and recruit their ECE programs to participate by emailing ECE program coordinators. Once 16 colleges agree to participate, allocation to the experimental and comparison conditions will occur. To safeguard the internal validity of the intervention, it is important to avoid randomly allocating individuals within each college to receive the training (or not), given the e-Learning course may be completed during pre-service ECEs’ class time and contamination may occur. As such, participating colleges/universities will act as the unit of randomization (i.e., clusters). Once consent has been obtained from the college/university representative (e.g., program coordinator/chair), the clusters will be stratified by province, college/university size, and college/university ECE program delivery mode (i.e., in-person, online, or blended learning). Blocked randomization will be performed to allocate clusters (1:1) using a computer-generated randomization tool (www.randomizer.org (accessed on 12 March 2022); the software will generate a number of 1 or 0) to either receive the training (experimental; “1”) or not (comparison; “0”).

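### College size is used to stratify the randomisation but is in no planned model, and the two outcome sections disagree on delivery mode; depending on how prognostic size is, this can widen the course-effect standard error and cost power

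*Protocol article*

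**What the plan says.** **Allocation.** Section 2.5.1 states that "the clusters will be stratified by province, college/university size, and college/university ECE program delivery mode", and then that "Blocked randomization will be performed to allocate clusters (1:1) using a computer-generated randomization tool". The number of colleges is given in two ways. Section 2.1 says they "will be randomly assigned to the experimental (*n* = 9) or comparison (*n* = 9) condition", while 2.5.1 says "Once 16 colleges agree to participate, allocation to the experimental and comparison conditions will occur". That discrepancy is a separate matter, but it means there are only 16 to 18 randomised units.

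**Primary analysis.** Section 2.12.1 plans "linear mixed effects models wherein group and time are our primary fixed effects". It adds demographic predictors for self-efficacy, knowledge, behavioural intention and perceived behavioural control. It says "we will explore the extent to which province/territory predicts the dependent variables, and whether there is a significant effect of previous training", and continues with program type and mode of delivery. Age, physical activity and sedentary time enter only if baseline differences are seen.

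**Secondary analysis.** Section 2.12.2 refers back to the primary approach but then says that "we will evaluate the extent to which early childhood education program type, and the province or territory in which the program is situated, impact" on the prediction models. Delivery mode is not repeated.

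**Size.** College size is not named in 2.12, 2.12.1 or 2.12.2, and it is not among the baseline variables in 2.10.1. It must nevertheless be known for every college before allocation.

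**The concern.** Stratifying on a prognostic factor removes its chance imbalance from the true variance of the group contrast. A model without that factor still counts its between-college variance as error. The reported standard error is then larger than the real one, the test is conservative, and the balance bought at randomisation does not become precision. With 16 to 18 colleges, between-college variance makes up most of the error, so this can matter.

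The article's rule for optional covariates makes it unlikely that size would come in later. Section 2.12 adjusts for baseline measures on which the groups differ. A factor balanced by design will tend not to differ, so the rule tends to leave it out. Province and delivery mode are mentioned, but as questions to explore or test, not as terms that stay in the model estimating the course effect.

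**Working it through.** **1. The plan's own figures (2.7).** D = 1 + (164 − 1) × 0.05 = 9.15. 112 × 9.15 / 0.70 = 1464 per group. 1464 / 164 = 8.93, so 9 colleges per arm. These figures reproduce and do not depend on the strata.

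**2. Strata against model terms.**

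| Stratifier (2.5.1) | 2.12.1 | 2.12.2 |
|---|---|---|
| Province | explored | evaluated |
| Delivery mode | tested for significance, also for intention and control | not repeated |
| College size | absent | absent |

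**3. Standard error for a contrast on post-course scores.** From the plan: ICC 0.05, 18 colleges, 164 × 0.70 ≈ 115 completers per college, alpha 0.025. Assumed: alpha is two-sided, colleges are of equal size, there are two size classes balanced between arms, and the college is the error unit. Let r be the share of between-college variance due to size (not given in the article, so a range is used). Let e be the remaining variance of a college mean.

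- With size in the model: A = (1 − r) × 0.05 + e.
- Without it, the balanced size sum of squares falls into the residual: U = (18/16) × r × 0.05 + (1 − r) × 0.05 + e.
- SE = √(2/9 × variance). The true sampling variance of the contrast is 2/9 × A in both cases.

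Setting (a): e = 0.95/115 = 0.00826. Setting (b) adds an assumed college-by-time variance of 0.01, so e = 0.01826.

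| r | (a) SE without / with size | ratio | (b) SE without / with size | ratio |
|---|---|---|---|---|
| 0 | 0.114 / 0.114 | 1.00 | 0.123 / 0.123 | 1.00 |
| 0.10 | 0.114 / 0.109 | 1.05 | 0.124 / 0.119 | 1.04 |
| 0.30 | 0.116 / 0.098 | 1.18 | 0.125 / 0.109 | 1.15 |
| 0.50 | 0.117 / 0.086 | 1.36 | 0.126 / 0.098 | 1.28 |

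**4. Type I error and power by simulation**, with size strata of 10 and 8 colleges. The difference of 0.41 SD is what 112 per arm detects with 80% power at alpha 0.025 without clustering.

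- Setting (a), power without / with size: 86.4 / 86.2% (r = 0), 87.0 / 89.1% (0.10), 88.6 / 94.7% (0.30), 90.4 / 98.3% (0.50). The loss is about 2 to 8 points for r from 0.10 to 0.50.
- Setting (b): the loss runs from about 2 points at r = 0.10 to 11–12 points at r = 0.50.
- Type I error without size, nominal 2.5%: in (a), about 2.0%, 1.1% and 0.3% at r = 0.10, 0.30 and 0.50; in (b), about 1.2–1.4% at r = 0.30.
- At d = 2 × √0.053 = 0.46, the two-arm equivalent of the plan's f² of 0.053, setting (a) gives 92.7 / 92.4% (r = 0), 93.3 / 94.4% (0.10), 93.9 / 96.9% (0.25) and 95.8 / 99.6% (0.50). The loss is at most about 4 points.

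**5. Sparse strata.** Suppose 2 sizes × 4 provinces × 3 modes = 24 cells for 18 colleges. Blocking then often cannot balance size. At r = 0.25, the type I error without size is 1.6%, against 1.2% when blocking is on size alone. The true SD of the contrast is 0.110 and the mean model SE is 0.117, so the overstatement shrinks but remains.

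**6. Group-by-time contrast.** If size shifts a college's scores equally at every time point, its change from baseline is (size + college + e₁) − (size + college + e₀) = e₁ − e₀, and size cancels. In setting (b), SE = √(2/9 × 2 × 0.01826) = 0.090 whatever r is. Simulated three-time-point models agree: the SE without / with a size main effect was 0.0891 / 0.0891 at r = 0, 0.0879 / 0.0879 at 0.30 and 0.0893 / 0.0893 at 0.50.

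**The case against.** The strongest reply is that the planned model covers three time points, and the abstract speaks of group differences across time points. If the course effect is the group-by-time contrast, a size main effect changes nothing unless size predicts change (step 6). This stands, and the fix has to depend on the contrast. It does not dispose of the point, because 2.12.1 names group and time as fixed effects and does not write out an interaction.

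Second, nothing in the article shows that size predicts scores, and 2.7 describes curricula as broadly similar across the country. This also stands: a reader might infer that the standard error is certainly too wide and power certainly lost, but the document supports only a conditional statement. The error is conservative, so false positives are not inflated.

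Third, a reader of 2.12.2 alone might infer that the secondary models omit delivery mode. Section 2.12.1 does not support that, because it applies mode of delivery to intention and perceived control as well. What remains is an inconsistency between the two sections.

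Fourth, three stratifiers across 16 to 18 colleges may leave about one college per stratum. The over-wide standard error is then smaller, but chance imbalance in size remains and no model corrects it. Keeping every stratifier at full detail would use too many college-level degrees of freedom, so the remedy must be sparse.

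Fifth, covariate lists are often left to an analysis plan. Here, however, the article gives its own list and its own inclusion rule, and these do not match its allocation.

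**Conclusion.** The point holds in conditional form. College size is a declared stratifier that no planned model contains. The other two stratifiers are not fixed as terms of the course-effect model, and 2.12.1 and 2.12.2 differ on delivery mode.

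For a group contrast on post-course scores with 18 colleges, size balanced by the blocking, and size explaining 10–50% of between-college variance, leaving it out makes the standard error about 5–30% larger (up to 36% with no college-by-time variation). It costs about 2 to 11 power points at 0.41 SD. At the plan's own effect size, setting (a) gives a loss of at most about 4 points, with power above 92%. The loss is nil if size is not prognostic, smaller if strata are sparse, and nil for a pure group-by-time contrast unless size predicts change. All of this rests on assumed values for the prognostic share, the two size classes and the college-by-time variance. The consequence is lost precision, not bias.

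**What to change.** In 2.12.1 and 2.12.2:

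- State which contrast is the course effect.
- Include college size as one term (the class used at randomisation, or log enrolment) in every course-effect model, regardless of significance or observed baseline differences. If the course effect is a group-by-time contrast, add a size-by-time term.
- List delivery mode in the same way in both sections.
- Enter province only in a coarse grouping that 16 to 18 colleges can support.

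This takes a few sentences and no new data, since the stratifiers are known at allocation. It uses one or two college-level degrees of freedom for size (with one term, 16 to 15 for 18 colleges) and two for three-level delivery mode, plus whatever the province grouping needs. If size is not prognostic, the power cost of the size term is trivial (86.4% to 86.2% at 0.41 SD in setting (a)).

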## 3. Discussion

A large body of research supports that the childcare environment, inclusive of ECEs’ programming, practices, and facilitation behaviours, can substantially influence children’s activity levels in this setting [4,48,49,50]. However, a gap in physical activity and sedentary behaviour-specific education has been noted to limit pre- and in-service ECEs’ confidence and ability to lead physical activity opportunities in childcare [10,19]. Providing pre-service ECEs with physical activity and sedentary behaviour-related training using an e-Learning platform is an innovative way to reach a large number of pre-service ECEs, while also making it easier to integrate into pre-existing early childhood education curricula. As such, the TEACH study represents a novel approach to population health that has the potential to advance pre-service training for ECEs across Canada.

In the interest of creating an evidence-informed physical activity intervention, the TEACH study was developed on the basis of Bandura’s Social Cognitive Theory [23] and Mayer’s Cognitive Theory of Multimedia Learning [31] for students with a variety of different learning styles. In addition, the e-Learning course content areas were derived following a rigorous Delphi method [51] with input from both physical activity and early childhood education experts [36]. These approaches not only ensure that the e-Learning course covers theoretically driven, relevant, and up-to-date content for promoting healthy activity behaviours in childcare, but they also verify that the course content is presented in line with pedagogy in the early years. Considering the involvement of stakeholders throughout the intervention process is linked to more effective implementation and higher adoption of behaviour change interventions [52], the participation of early childhood education stakeholders from the beginning of the TEACH study sets the intervention up for greater success. Further, piloting the e-Learning course with both pre- and in-service ECEs, and gathering input on its functionality through the application of the EESS model, will ensure a high-quality e-Learning experience is provided to students. With more post-secondary institutions shifting toward online class offerings [53], the TEACH study will deliver a timely and fitting solution to address the curriculum gap in physical activity and sedentary behaviour within early childhood education programs.

Other interventions have been developed to better support ECEs in promoting active behaviours among young children [26,29]; however, this is the first study to target pre-service training via an online platform. Pate et al. [26] recently incorporated physical activity training for educators into a childcare intervention, and preschoolers increased their energetic physical activity by 4 min/day. Even more promising, a feasibility study with the educators involved in Pate and colleagues’ project (*n* = 17) showed that they reported higher knowledge and self-efficacy to lead physical activity opportunities following the intervention, while also communicating that they would use the knowledge they gained in future programming [54]. As such, there is great potential for training interventions to make a difference in the physical activity experiences offered in childcare settings. However, the effectiveness of such training at the pre-service level needs to be explored, as this is the best platform to target all future ECEs. 

## 4. Conclusions

Utilizing e-Learning platforms to complement pre-service ECEs’ post-secondary education is a forward-thinking approach to ensure future ECEs receive necessary health promotion education. If successful, ECE graduates will enter their profession with greater self-efficacy to engage young children in physical activity and reduce sedentary behaviours during childcare hours, which is likely to increase the quantity and quality of programming offered to children in their care. Moreover, offering pre-service ECEs this training online improves reach. If effective, we will translate the e-Learning course into French to easily be employed by colleges/universities across Canada, and will support its adoption in countries where movement guidelines for the early years are similar to Canada’s (e.g., Australia, New Zealand; [55,56]). This protocol paper offers a detailed account of the TEACH study and tools for future investigations which aim to increase ECEs’ physical activity-related knowledge and self-efficacy via e-Learning. The results of the TEACH study will be shared with early years physical activity researchers globally and disseminated to Canadian colleges/universities with early childhood education programs, early years policymakers, childcare staff and directors, as well as other key stakeholders to ensure those responsible for the programming and practices within the childcare environment have the knowledge necessary to make decisions in support of healthy active behaviours among young children.

## Figures and Tables

**Figure 1 ijerph-19-03890-f001:**
[figure not shown]
Breakdown of the TEACH study e-Learning course, by module.

**Table 1 ijerph-19-03890-t001:** Tools Used in the TEACH Study.

		Experimental Group			Comparison Group		
		Baseline	Post	3-Month Follow-Up	Baseline	Post	3-Month Follow-Up
Pilot Study							
Pilot Test Participants	Consent	X					
	Demographic Survey	X					
	Self-Efficacy Questionnaire	X	X				
	Knowledge Questionnaire	X	X				
	Behavioural Intention and Control Survey	X	X				
	Process Evaluation Survey		X				
	Interview		X				
Quasi-Experimental Study							
University/College	Consent	X			X		
	Curriculum Review	X			X		
Instructors	Consent	X					
	Process Evaluation Survey		X				
	Interview		X				
Pre-Service ECEs	Consent	X			X		
	Demographic Survey	X	X		X	X	
	Self-Efficacy Questionnaire	X	X	X	X	X	X
	Knowledge Questionnaire	X	X	X	X	X	X
	Behavioural Intention and Perceived Behavioural Control Survey	X	X	X	X	X	X
	Process Evaluation Survey		X				
	Interview		X				
Research Team	Website Metrics	X	X				
	CFIR Checklist	X	X	X	X	X	X

TEACH = Training pre-service EArly CHildhood educators in physical activity; ECE = early childhood educator; CFIR = Consolidated Framework for Implementation Research.

## Data Availability

Not applicable.

## Abbreviations

MVPA	Moderate-to vigorous-intensity physical activity
ECE	Early Childhood Education
EESS	Evaluating e-Learning System Success
TEACH	Training pre-service EArly CHildhood educators in physical activity
CFIR	Consolidated Framework for Implementation Research

## Appendix A

**Pre-Service ECEs’ Physical Activity and Sedentary Behaviour-Related** **Knowledge Survey—Sample**
The following questions will test your knowledge of the Canadian 24-h Movement Guidelines for the Early Years (0–4 years):
1. How many minutes of tummy time are infants (<1 year) recommended to engage in each day? ⚪ 10 min (1) ⚪ 20 min (2) ⚪ 30 min (3) ⚪ 40 min (4)
2. How many minutes of total physical activity (i.e., any intensity physical activity) are toddlers (1–2 years) and preschoolers (3–4 years) recommended to engage in each day? ⚪ 60 min (1) ⚪ 90 min (2) ⚪ 120 min (3) ⚪ 180 min (4)
3. How many minutes of moderate-to-vigorous physical activity (i.e., higher intensity physical activity) are preschoolers (3–4 years) recommended to engage in each day? ⚪ 30 min (1) ⚪ 60 min (2) ⚪ 90 min (3) ⚪ 120 min (4)
4. How many minutes of screen time should a 3-year-old be limited to each day? ⚪ 30 min (1) ⚪ 60 min (2) ⚪ 90 min (3) ⚪ 120 min (4)
5. How much good-quality sleep, including naps, should infants (4–11 months) get each day? ⚪ 10–13 h (1) ⚪ 11–14 h (2) ⚪ 12–16 h (3) ⚪ 14–17 h (4)
6. How much good-quality sleep, including naps, should toddlers (1–2 years) get each day? ⚪ 10–13 h (1) ⚪ 11–14 h (2) ⚪ 12–16 h (3) ⚪ 14–17 h (4)
The following questions will test your knowledge of research-based recommendations for physical activity and screen-viewing at childcare:
7. For full-day programs (8 h), what is the recommendation for preschoolers’ (3–4 years) physical activity while in care? ⚪ 60 min/day of total physical activity, 20 min of which is at a moderate-to-vigorous intensity (1) ⚪ 90 min/day of total physical activity, 30 min of which is at a moderate-to-vigorous intensity (2) ⚪ 120 min/day of total physical activity, 40 min of which is at a moderate-to-vigorous intensity (3) ⚪ 180 min/day of total physical activity, 60 min of which is at a moderate-to-vigorous intensity (4)
8. What is the recommendation for screen-viewing in childcare? ⚪ There are no screen-viewing limits (1) ⚪ Limit screen-viewing to 30 min/day (2) ⚪ Screen-viewing is only recommended for educational purposes (3) ⚪ Screen-viewing is not recommended (4)

**End of Block: Knowledge—Guidelines**

**Start of Block: Knowledge—Definitions**

The following questions will assess your knowledge of common terms related to physical activity and sedentary behaviour among young children.
9. Galloping, hopping, and jumping are examples of what type of fundamental movement skill? ⚪ Stability (1) ⚪ Locomotor (2) ⚪ Manipulative (3) ⚪ Isometric (4)
10. What is an example of a muscle and bone-strengthening activity? ⚪ Playing catch (1) ⚪ Kicking a ball (2) ⚪ Balancing on a bench (3) ⚪ Jumping rope (4)
11. The “motivation, confidence, physical competence, knowledge, and understanding to value and take responsibility for engagement in physical activities for life” is the definition of what? ⚪ Structured physical activity (1) ⚪ Active lifestyle (2) ⚪ Physical literacy (3) ⚪ Active play (4)
12. What type of play is “a form of gross motor or total body movement in which young children use energy in a fun and freely chosen manner”? ⚪ Outdoor play (1) ⚪ Loose parts play (2) ⚪ Risky play (3) ⚪ Active play (4)
13. What type of play invites curiosity by allowing children to play with everyday items (such as kitchen utensils and cardboard boxes) or natural elements (such as tree stumps or pebbles)? ⚪ Outdoor play (1) ⚪ Loose parts play (2) ⚪ Risky play (3) ⚪ Active play (4)
14. What practice can be used to limit sedentary time while waiting for the next activity or travelling to a different part of the classroom? ⚪ Active breaks (1) ⚪ Active learning (2) ⚪ Active transitions (3) ⚪ Active play (4)
15. What is not considered a category of risky play? ⚪ Play at heights (1) ⚪ Play with tools (2) ⚪ Play near elements (e.g., water, fire) (3) ⚪ Play with loose parts (4)

